#### Primary Outcomes

The study includes 2 co-primary outcomes:

The immediate posttreatment change in the FRP measured using sEMG.The immediate posttreatment change in pain intensity measured using a 100-mm VAS.

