### Statistical Analysis

Baseline characteristics will be assessed using Fisher exact test, ANOVA, and the Levene test. To evaluate the primary and secondary outcomes, we will use a linear mixed-effects model to account for the variability between groups and over time. This model will include “treatment group,” “time,” and their interaction as fixed effects. To address the potential influence of practitioner-related differences, “practitioner ID” will be included as a random effect. For post-hoc analyses, the Bonferroni correction will be applied to adjust for multiple comparisons. For nonnormally distributed data, the Mann-Whitney *U* test, Friedman test, or Kruskal-Wallis test will be used as appropriate. Blinding success will be evaluated by comparing the proportion of correct guesses in each group against chance level (33.3%) using a chi-square goodness-of-fit test. In addition, Bang Blinding Index will be calculated for both participants and acupuncturists to quantify the degree of blinding [55,57]. A Blinding Index close to 0 indicates successful blinding, whereas values approaching ±1 indicate unblinding. To account for variability among acupuncturists, analyses will be conducted under an intention-to-treat framework. Missing outcome data will be handled using multiple imputation under the assumption of missing at random. All statistical analyses will be conducted using SPSS Statistics version 31 (IBM SPSS Statistics) and R (R Foundation for Statistical Computing). Statistical significance will be set at a 2-sided *P* value of <.05.

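### The fallback for non-normal data lets the observed distribution decide the test, drops the planned practitioner term and lists Friedman, which cannot compare arms

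*Protocol article*

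**What the plan says.** All of the analysis text is in the protocol article, Statistical Analysis.

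- Main method: "To evaluate the primary and secondary outcomes, we will use a linear mixed-effects model to account for the variability between groups and over time". The model has treatment group, time "and their interaction as fixed effects".
- Practitioner: "To address the potential influence of practitioner-related differences", practitioner ID "will be included as a random effect". Recruitment gives seven acupuncturists.
- Fallback: "For nonnormally distributed data, the Mann-Whitney" U test, "Friedman test, or Kruskal-Wallis test will be used as appropriate". The sentence names no outcome and no contrast. Its trigger is the distribution of the data, not of the model residuals.

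Two other places fix the question that the analysis must answer. The Introduction sets a between-arm aim: whether penetrating needles improve FRP and pain more than each of the two placebos. Primary Outcomes defines both co-primary outcomes as an immediate pre-post change, for example "The immediate posttreatment change in the FRP measured using sEMG". The later VAS ratings, which make five time points in all under Primary Self-Report Measurement, are secondary.

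**The concern.** The plan names one model for every primary and secondary outcome, then supplies a way out of it that is used once the data have been seen. An sEMG measure and a bounded 0-100 VAS could plausibly look non-normal, so the way out may well be taken. Results reports that data collection ended in March 2025, while the analysis is still described in the future tense.

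Three things are at stake. The choice of primary test would depend on observed outcomes. The practitioner term, included on purpose, would be lost. And one of the three listed tests, Friedman, answers whether scores changed over time, not whether arms differ. The trigger is also misplaced: a linear mixed model relies on approximately normal residuals and random effects, not on normal raw data.

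**Working it through.** **The plan's own figure.** The fallback does not bear on sample size, but the stated figure reproduces. Inputs from Sample Size: effect size 0.51, power 95%, alpha 5%, three groups. Taking 0.51 as Cohen's f in a one-way ANOVA, the noncentrality is N x f^2 = 63 x 0.2601 = 16.39, which gives power 0.952. N = 62 gives 0.948, so 63 is the smallest N.

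**1. Do Kruskal-Wallis and Mann-Whitney answer the between-arm question?** For the co-primary outcomes they can. With two time points, the group-by-time F test is identical to a one-way ANOVA on the change score. A numerical check on invented data (25 per arm) gave F = 10.4047 by both routes. A rank test on the change score is therefore the rank analogue of the interaction, and it uses baseline.

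A simulation tested how this behaves. Its assumptions are not from the documents: 25 per arm, skewed errors, total SD 1, within-person correlation 0.5, baseline plus three later measurements, 1,500 runs per scenario. With no arm difference, the rejection rate at the 5% level was 0.036 to 0.053 for Kruskal-Wallis on change and 0.039 to 0.055 for Mann-Whitney. With an assumed 0.8 SD benefit of penetrating needles and no practitioner variation, power was 0.946 and 0.919.

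Neither test gives a joint group-by-time test over the five VAS times.

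**2. What does losing the practitioner term cost?** In the same simulation, seven practitioners with an assumed SD of 0.5 were allocated independently of arm.

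| Test on change | No arm difference | 0.8 SD effect, practitioner SD 0 | 0.8 SD effect, practitioner SD 0.5 |
|---|---|---|---|
| Kruskal-Wallis | 0.053 (practitioner SD 0.5) | 0.946 | 0.846 |
| Mann-Whitney | 0.055 (practitioner SD 0.5) | 0.919 | 0.812 |

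Size held and power fell by 0.10 to 0.11. The two power columns compare no practitioner variation with variation that is ignored, so the drop indicates roughly the most that a practitioner term could win back.

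**3. What does Friedman test?** With identical arms and a common 0.4 SD improvement, Friedman on the pooled sample rejected in 100% of runs. It detects the shared change and is blind to arm. Run arm by arm, it gave discordant verdicts (some arms significant, others not) in 52% of runs at that shift. The figure was 14% with no shift and 0.1% at 0.8 SD, where nearly every arm is significant.

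**4. Illustration for a pre-post comparison.** With two time points Friedman reduces to a sign test. For n = 25 the statistic is (2B - 25)^2 / 25, where B is the number who improve. B = 17 gives 3.24 and B = 18 gives 4.84, against a critical value of 3.84, so it rejects at B of 18 or more, or 7 or fewer. For a normal change of 0.5 SD of within-person change, the probability of improving is 0.6915 and the power in one arm is p = 0.4745. With three independent arms that truly improve equally:

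- penetrating significant, at least one placebo arm not: p(1 - p^2) = 0.4745 x (1 - 0.2252) = 0.368;
- penetrating significant, neither placebo arm significant: p(1 - p)^2 = 0.4745 x 0.5255^2 = 0.131.

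For true changes of 0.4, 0.6 and 0.7 SD, the first probability is 29%, 38% and 32%, and the second is 15%, 9% and 4%.

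**The case against.** The strongest reply is that the sentence commits to less than it seems to. It does not say that rank tests stand in for the model, and it could cover the MASS or the guess-confidence ratings. It leaves room for a sensible assignment, with Friedman for repeated measures and the other two for comparisons between arms. A separate analysis plan may settle which test goes where. This stands in part. Replacement is still the natural reading, because the sentence follows directly on the model for primary and secondary outcomes and exempts none of them. The point rests on that stated rule, not on missing detail.

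Four stronger readings are tempting, and the documents do not support them.

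- A reader might infer that all three tests ignore baseline and give no interaction. The co-primary outcomes are change scores, so Kruskal-Wallis and Mann-Whitney on change escape both criticisms.
- A reader might infer that Friedman will be run in each arm and the pattern read as efficacy. The article does not say so, and its aim is between-arm. The 37% and 13% show only what such use would risk.
- A reader might infer that dropping practitioner inflates false positives. With practitioner independent of arm it did not.
- A reader might infer a clash with the statement "Missing outcome data will be handled using multiple imputation under the assumption of missing at random", since rank tests do not ordinarily give an estimate and standard error to pool. The article does not say that rank results will be pooled across imputations.

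**Conclusion.** The point holds in limited form. The article states a fallback that depends on the raw data, removes the practitioner term and includes a test that cannot address the between-arm aim. For the two co-primary outcomes, two of the three tests would still give a valid comparison of arms if applied to change. The loss there is precision, about 0.10 in power under an assumed practitioner SD of 0.5 and an assumed effect of 0.8 SD. The more serious risk is Friedman. If it were used arm by arm in the pre-post setting, equal true improvement of 0.5 SD would give a misleading pattern in about 37% of trials (at least one placebo arm not significant) or 13% (both not). Those figures assume n = 25 per arm, normal changes and a use of the test that the text permits but does not state. The wording should be corrected before the analysis is run.

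**What to change.** In Statistical Analysis, replace the fallback sentence with four statements.

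1. The stated mixed model (group, time, interaction, practitioner) is the primary analysis whatever the raw distribution, and its fit is judged on residuals.
2. A permutation or bootstrap version of the same arm contrast is the sensitivity analysis. A transformation is an option only if the FRP metric allows it, since the article does not define that metric's scale.
3. If simple rank tests are kept, they are supportive only and limited to between-arm tests on change scores.
4. Neither Friedman nor any other within-arm test is used to support efficacy.

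The cost is wording and a little code. The sample size is unchanged. A transformed outcome, if used, would need a line on how to read the result.

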### Randomization

In total, 75 sets of double-blind needles were prepared and placed in separate bags numbered 1-75 (25 sets of 40 penetrating acupuncture needles, 25 sets of 40 skin-touch acupuncture needles, and 25 sets of 40 no-touch acupuncture needles). Seventy-five participants were randomly assigned 1:1:1 to the penetrating needle group, the skin-touch needle group, or the no-touch needle group by an independent investigator using a random numbers table that was generated by the RAND function (Microsoft Office Excel 2007).

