### Secondary Self-Report Measurement

The following validated questionnaires were used to assess physical disability and acupuncture-related sensations at the specified time points.

RMDQ: the RMDQ assesses physical disability and was completed at baseline and one week after.JOABPEQ: the JOABPEQ assesses physical disability with social life and their psychological effects, and it was completed at baseline and one week after.MASS: the MASS consists of 12 descriptors of sensations to qualify and quantify acupuncture sensations. Participants select up to 12 descriptors that describe the sensations they had during their acupuncture treatment and then rate the intensity of these sensations on a numeric rating scale (NRS) from 0 (none) to 10 (strongest imaginable). If participants felt other sensations in addition to the 12 descriptors, they wrote a description of the additional sensation and rated it on the NRS [64,65]. The MASS was completed right after the acupuncture treatment was complete.Blinding assessment: the practitioner and patient guess at the needle’s authenticity. The participants guessed whether the needle type was “penetrating,” “skin-touch,” “no-touch,” or “cannot identify the needle type” right after the acupuncture treatment was complete. The acupuncturists were also asked to guess the needle type and rated their confidence in their guess.

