After 15 minutes, the acupuncturist withdrew each needle to its initial position using an alternating twirling technique to remove them [38-45,54,66]. The needle was then stored in an opaque envelope to prevent the group allocation from being revealed. After all needles were removed, the research assistant checked for bleeding from each needled insertion site and wiped the blood away with a cotton ball and/or applied pressure if needed. The acupuncturist again massaged the area where the needle was inserted.

Then, the acupuncturist assessed the participant for back pain. If the participant had no pain, the treatment was complete. If the participant still had pain, the hardest indurations and the most tender areas in the lumbar erector spinae, quadratus lumborum, gluteus medius, and biceps femoris were treated using a Sparrow Pecking technique (rapidly inserting and withdrawing the needle tip within a 2 mm amplitude) using another needle from the same set of needles randomly assigned to the participant [13].

After the acupuncture treatment was complete, participants rated the intensity of their LBP on a 100 mm VAS. Participants then completed the MASS. The participants then guessed whether the treatment was “penetrating,” “skin-touch,” “no-touch,” or “cannot identify the needle type.” They reported their confidence level in their guesses on a 100 mm VAS ranging from 0 (no confidence) to 100 (full confidence) [37-43,52,63]. The acupuncturists were also asked to guess the needle type and rated their confidence in their guess. The sEMG of the lower back was recorded using the same procedure as before the intervention. One week after treatment, participants brought the completed questionnaires (intensity of LBP on VAS, RMDQ, and JOABPEQ) back to the Acupuncture Clinic. At that time, a research assistant offered them a free acupuncture treatment with regular acupuncture needles.

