### Recruitment

Seven licensed, experienced acupuncturists (4 are listed as authors: [name]) with more than 5 years of experience each, at TAU Acupuncture Clinic, administered the acupuncture treatments. We enrolled 75 participants with CNSLBP. Participants were recruited by advertisements listed on TAU websites, flyers placed on TAU campus notice boards, and at public facilities (city offices, gymnasiums, and surrounding high-rise apartment buildings). The advertisements provided a brief introduction to the study, a description of the target population with eligibility criteria, and study contact information. Participant recruitment began in October 2018.

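### Testing correct guesses in each arm against 33.3% confounds a shared guessing preference with unblinding

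*Protocol article*

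**What the plan says.** Under Statistical Analysis, the protocol article fixes the test and its reference value: "Blinding success will be evaluated by comparing the proportion of correct guesses in each group against chance level (33.3%) using a chi-square goodness-of-fit test". It adds a second measure, "In addition, Bang Blinding Index will be calculated for both participants and acupuncturists to quantify the degree of blinding", and a rule for reading it: "A Blinding Index close to 0 indicates successful blinding, whereas values approaching ±1 indicate unblinding". The significance level is two-sided 5%.

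Under Treatment Procedure the answer options are given: "The participants then guessed whether the treatment was “penetrating,” “skin-touch,” “no-touch,” or “cannot identify the needle type". Under Secondary Self-Report Measurement, "The acupuncturists were also asked to guess the needle type and rated their confidence in their guess". Under Randomization, "Seventy-five participants were randomly assigned 1:1:1 to the penetrating needle group, the skin-touch needle group, or the no-touch needle group", which makes 25 per arm. The article nowhere states a comparison of guesses between arms.

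**The concern.** Blinding holds when the guess is independent of the arm. Within a single arm, a correct guess is just a guess that names that arm's needle, so the proportion correct mixes two things: knowledge of the allocation, and any general inclination towards one answer. Comparing it with a fixed one third treats both as the same departure. An inclination is plausible here, because the script under Treatment Procedure tells every participant that one of the three groups receives real needles.

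Blinding of both patient and practitioner is the trial's main methodological claim, and the guesses are a listed secondary outcome. A check that cannot tell preference from knowledge could discredit blinding that worked, or leave unblinding in a placebo arm unremarked.

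**Working it through.** **Inputs.** From the article: 25 per arm (Sample Size, Randomization), reference value 33.3% and two-sided 5% (Statistical Analysis). Assumed, because the article gives none: the shares of guesses, and that everyone names a needle type.

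**The plan's figure.** 1/3 = 33.3%. This is the chance of a correct guess if the three types are named equally often and nobody answers that they cannot identify the needle.

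**What the per-arm test tests.** Let the guess be independent of arm, with shares q1, q2, q3 for penetrating, skin-touch and no-touch. The expected proportions correct in the three arms are then q1, q2, q3. The null of 1/3 in each arm is a statement that guesses are evenly spread. Independence does not imply it.

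**Rejection region.** With x correct out of n = 25, X² = (x − n/3)²/(n/3) + ((n − x) − 2n/3)²/(2n/3), and the 5% critical value on 1 df is 3.84. X² is 5.12 at x = 3, 3.38 at x = 4, 2.42 at x = 12 and 3.92 at x = 13. The test rejects at 3 or fewer, or 13 or more.

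**Perfect blinding, exact binomial probabilities:**

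| Share naming penetrating in every arm (rest split equally) | Penetrating arm rejects | Each placebo arm rejects |
|---|---|---|
| 1/3 | 5.6% | 5.6% |
| 40% | 16% | 5% |
| 50% | 50% | 10% |
| 60% | 85% | 23% |

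Example: every arm gives 15 penetrating, 5 skin-touch and 5 no-touch guesses. The three rows of the table are identical, so the guesses say nothing about allocation. Yet the penetrating arm gives X² = (15 − 8.33)²/8.33 + (10 − 16.67)²/16.67 = 5.33 + 2.67 = 8.0, p = 0.005.

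**Some real knowledge.** Let 25% know their arm and the rest name the penetrating needle 60% of the time and each placebo type 20%.
- Penetrating arm: 0.25 + 0.75 × 0.60 = 0.70 correct, rejection 98% (85% with no knowledge).
- Each placebo arm: 0.25 + 0.75 × 0.20 = 0.40 correct, rejection 16%.
- For comparison, with even guessing among the rest: 0.25 + 0.75/3 = 0.50 correct, rejection 50% in each arm.

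The preference thus cuts the chance of a signal in a placebo arm from 50% to 16%. The strong signal in the penetrating arm would mostly be there anyway.

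**The index.** The article gives no formula. With c the proportion correct, the two-category form 2c − 1 gives +0.2, −0.6, −0.6 for shares 60/20/20 under perfect blinding. A form rescaled to one-third chance, (c − 1/3)/(2/3), gives +0.4, −0.2, −0.2. Either way, a positive value in the penetrating arm with negative values in the placebo arms arises from a shared belief alone.

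**A test of association.** The chi-square test on the 3 × 3 arm-by-guess table (20,000 simulations) rejects 4.9% and 5.1% of the time under perfect blinding with 50% and 60% naming penetrating. With 25% true knowledge and the 60% preference its power is about 74%. A permutation test on total correct guesses, shuffling the 25/25/25 labels, rejects 3.5% to 4.5% under blinding and has about 89% to 91% power with 25% true knowledge. A check of these last figures (3,000 simulated trials, 999 permutations, preference 50% or 60%) reproduced them for a one-sided test, 88% and 91%. Doubling the smaller tail for a two-sided test gave 81% and 85%.

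**The case against.** The strongest reply is that the per-arm test does respond to real unblinding. With 60% correct in every arm, each arm rejects 85% of the time. That stands. A reader might infer that the test ignores whether guesses track allocation, but it does not. The fault is that it cannot separate tracking from preference.

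Second, the article does not say that one rejected arm means failed blinding, and the index is reported beside the test. A reader might go further and conclude that a shared belief would formally be declared unblinding. The text says only how success will be evaluated, so that is an inference. For this reason the size is given per arm and not as the chance that any arm rejects.

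Third, a reader might infer from the ±1 sentence that a shared belief would be reported as unblinding everywhere. That needs near-unanimous guessing and the 2c − 1 form. At 60/20/20 neither form clearly approaches ±1.

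Fourth, guesses come from "Seven licensed, experienced acupuncturists", and one might expect their personal habits to make matters worse. They do not materially: simulated rates of at least one rejection were 0.604 and 0.898 with individual preferences, against 0.592 and 0.912 without. The article also names acupuncturists only for the index and does not say that the goodness-of-fit test covers them.

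Finally, the guess shares are assumed, and part of the low placebo-arm power comes from having only 25 per arm. Both are true and limit the size, not the principle.

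**Conclusion.** The point holds: the stated test confounds a shared guessing preference with unblinding, and the reading of the index has the same weakness. Its practical size depends on guess shares that the article does not give. It is slight at 40% naming the penetrating needle (16% rejection in that arm) and severe at 60% (85%), assuming 25 per arm and everyone naming a type. Nor does the pattern across arms rescue the check: with the 60% preference, 98% against 85% in the penetrating arm and 16% against 23% in each placebo arm give little to tell 25% true knowledge from none.

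The consequence is confined to the blinding assessment. No primary test, treatment estimate or sample size depends on it. It should still be changed, because this check supports the trial's central claim.

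**What to change.** Make the main blinding test one test of association between guess and allocated arm, done separately for participants and acupuncturists. Keep the answer that the needle cannot be identified as its own category wherever it was offered. Either of two forms will do:

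- an exact or chi-square test on the arm-by-guess table, which picks up any dependence of guess on arm; or
- a permutation test on total correct guesses with the 25/25/25 labels shuffled, which has more power when people truly know their arm. State whether it is one- or two-sided, since the section sets a two-sided level.

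Report the per-arm proportions and Bang indices as description, read jointly across arms. Reword the ±1 sentence to say that a positive value in the penetrating arm with negative values in the placebo arms can reflect a shared belief in the real needle and is not by itself evidence of unblinding.

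The cost is wording only, since the guesses are already collected. Data collection is complete, so the change should be dated and should state whether the guesses had been tabulated by arm beforehand. One small downside: a single test does not show which arm was unblinded, so the full arm-by-guess table should still be shown.

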### Sample Size

We calculated effect sizes and sample sizes using G*Power 3.1.9.6 (Heinrich-Heine-Universität, Düsseldorf). Results from a previous study of CNSLBP that determined the effects of high-velocity spinal manipulation on paraspinal muscle activity with sEMG found an effect size of 0.51 [46]. Based on this effect size, with a statistical power of 95% and an alpha of 5%, the sample size was calculated to be 63 participants (21 participants in each group). However, in our study, we conduct X-ray examinations at TAU Medical Clinic as a screening test for CNSLBP. Therefore, with a potential dropout rate of 20%, we recruited a total of 75 participants (25 participants in each group).

Because prior randomized trials evaluating acupuncture effects on FRP are lacking, the effect size was derived from the most physiologically comparable intervention study examining paraspinal muscle activity. The target power was set at 95% to reduce the probability of Type II error and to enhance the stability of the estimate in this mechanistic trial.

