### Conclusions

This study has several distinctive methodological features, as outlined below:

This study is the first randomized double-blind (acupuncturist-participants) placebo-controlled trial to test the short-term effects of acupuncture on CNSLBP.This study uses a genuine penetrating needle and 2 placebo needles, a skin-touch needle and a no-touch needle that is physiologically inert, to better understand the key component of acupuncture.This study evaluates the effects of acupuncture on CNSLBP using both self-report measurement (pain intensity) and an objective measurement (activation of the erector spinae muscles using surface electromyography).

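### A non-significant per-arm test of guesses against 33.3% cannot show that blinding succeeded in arms of 25, and 33.3% is not the chance level once a 'cannot identify' answer is allowed

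*Protocol article*

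**What the plan says.** Statistical Analysis fixes the method: "Blinding success will be evaluated by comparing the proportion of correct guesses in each group against chance level (33.3%) using a chi-square goodness-of-fit test". The general significance rule in the same section is "Statistical significance will be set at a 2-sided *P* value of <.05". The unit is the single arm. Randomization states that "Seventy-five participants were randomly assigned 1:1:1 to the penetrating needle group, the skin-touch needle group, or the no-touch needle group", and Sample Size gives 25 per arm, with a 20% dropout allowance.

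A second measure follows: "Bang Blinding Index will be calculated for both participants and acupuncturists to quantify the degree of blinding". Its reading is given as "A Blinding Index close to 0 indicates successful blinding, whereas values approaching ±1 indicate unblinding". Neither the test nor the index carries a cut-off, margin or confidence interval in the text.

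Secondary Self-Report Measurement and Treatment Procedure offer participants four answers: the three needle types and "cannot identify the needle type". Participants also rate confidence in their guess on a 100 mm scale. Acupuncturists guess the needle type and rate their confidence as well; whether they too have the fourth answer is not stated.

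**The concern.** Successful blinding means that guesses are no better than chance, which is the null hypothesis of the planned test. Such a test can show unblinding when it rejects. It shows nothing in favour of blinding when it does not reject, unless the arm is large enough to exclude unblinding that matters.

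The null value raises a second problem. One third is the chance of a correct answer for someone who must pick one of three. A participant who may decline to pick is correct less often by chance if a declined answer counts as wrong.

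Blinding is central to this trial. The Conclusions state: "This study is the first randomized double-blind (acupuncturist-participants) placebo-controlled trial to test the short-term effects of acupuncture on CNSLBP". One of the two co-primary outcomes is self-reported pain on a VAS, and participants are told before treatment that all three needle types exist. Whether the pain result can be read as free of expectation effects depends on how this assessment is interpreted.

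**Working it through.** The protocol gives no power or precision for the blinding assessment. Its one figure, 33.3%, is 1/3: three needle types, one of them correct.

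**Inputs.** From the protocol: n = 25 per arm, null 1/3, two-sided 0.05, 20% dropout (25 × 0.8 = 20). Assumed here: a share k of an arm knows the needle and the rest guess evenly among three, so the proportion correct is p = k + (1 − k)/3. For k = 0.25, p = 0.25 + 0.75/3 = 0.50.

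**Non-rejection region at n = 25.** Expected counts are 8.33 correct and 16.67 not correct. With x correct, χ² = (x − 8.33)²/8.33 + (x − 8.33)²/16.67 on 1 df, without continuity correction.

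| Correct | χ² | P |
|---|---|---|
| 3 | 5.12 | .024 |
| 4 | 3.38 | .066 |
| 12 | 2.42 | .12 |
| 13 | 3.92 | .048 |

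Counts of 4 to 12 (16% to 48%) are therefore non-significant. The actual size of the test is 5.6%. At 12 of 25 the Wilson 95% interval is 30% to 67%. Its upper end corresponds to k = (0.665 − 0.333) × 1.5 ≈ 0.50, so about half the arm could know.

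**Miss rate in one arm** = P(4 ≤ X ≤ 12), X ~ Binomial(25, p):

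| Share knowing k | p | Missed |
|---|---|---|
| 0.10 | 0.40 | 84% |
| 0.20 | 0.467 | 63% |
| 0.25 | 0.50 | 50% |
| 0.30 | 0.533 | 37% |
| 0.40 | 0.60 | 15% |

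At k = 0.25, a continuity-corrected or exact test misses 65%. With 20 participants the uncorrected test misses 59%. About 71 per arm would be needed to hold 80% power at p = 0.50.

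**Bang index.** For a chance-corrected index on three options, (p − 1/3) × 1.5 (the scaling is assumed), the 95% half-width near chance is 1.5 × 1.96 × √[(1/3)(2/3)/25] ≈ 0.28. An observed value of 0 is thus compatible with a quarter of the arm knowing.

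**The 'cannot identify' answer.** Let a share d of those without knowledge give it, counted as incorrect. Then p = k + (1 − k)(1 − d)/3.

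| d | k | p | Test rejects |
|---|---|---|---|
| 0.20 | 0 | 0.267 | 7.5% |
| 0.20 | 0.25 | 0.45 | 31% |
| 0.40 | 0 | 0.20 | 23% |
| 0.40 | 0.25 | 0.40 | 16% |

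At d = 0.40 the test rejects more often under pure guessing (23%, because correct answers are too few) than when a quarter know (16%). If those answers are instead left out of the denominator, the chance level among those naming a needle returns to 1/3, and power at k = 0.25, d = 0.40 is 56%.

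**The case against.** The protocol nowhere says that a non-significant result will be taken as proof of blinding. A reader might infer that from the way success is tied to the test, but it is not a stated rule. Nor is the test the only tool: the Bang index is planned for both participants and acupuncturists, and confidence in the guess is collected. An analysis plan that is not shown may set interpretation limits. Guess data are a secondary outcome, and the other co-primary, surface electromyography, is less exposed to expectation.

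The size of the problem can also be overstated. The 50% is per arm: if a quarter knew in all three arms, all three tests would be non-significant in 0.5³ = 12.5% of trials. At 60% correct, one arm is missed only 15% of the time. The 'cannot identify' answers do not worsen matters under every counting rule; excluding them raises power slightly.

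These limits stand, and they restrict the point to single arms and to what a non-significant result can support. They do not remove it. The test, its null value and its per-arm use are fixed in the text rather than left open, and an index read as close to 0 is too imprecise at this size to fill the gap.

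**Conclusion.** The point holds in a limited form. With 25 per arm, a non-significant goodness-of-fit test cannot support a claim of successful blinding. It is compatible with up to about half of an arm knowing, and it misses a quarter knowing 50% of the time in that arm (59% at n = 20). The Bang index as described does not change this. The 33.3% null is right only if every respondent names a needle type, or if other answers are excluded.

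The miss rates rest on the model of some knowing and the rest guessing evenly. The 'cannot identify' figures rest on an assumed 20% or 40% use of that answer, counted as incorrect. The documents do not support the stronger readings that the plan declares non-significance to be proof, or that the trial as a whole would miss such unblinding half the time.

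**What to change.** In Statistical Analysis:

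1. State that a non-significant test against chance is not evidence of successful blinding.
2. Report the proportion correct and the Bang index per arm with 95% confidence intervals, separately for participants and acupuncturists. Base the conclusion on those intervals, and describe blinding as not established where they include substantial unblinding.
3. Either apply the 33.3% comparison only to those who name a needle type, or state how 'cannot identify' answers are counted and adjust the chance level to match.

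The verdict should not rest on a proportion pooled over arms. For example, a rule that the pooled Wilson upper limit (n = 75) lie below 50% is met with 29 or fewer correct. It would declare blinding maintained 54% of the time when a quarter know in one arm only, and 30% of the time at 60% correct in one arm (the others at chance), where the planned test misses 15%. With 80%, 10% and 10% correct it would do so 94% of the time.

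The cost is analysis wording, with no new data. The downside is that at this sample size the blinding claim may well end as inconclusive.
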